## Abstract

The aim of our study will be to evaluate the effect of combining pelvic floor muscle training (PFMT) with the urgency-suppression technique and silodosin in comparison with silodosin alone in men with Benign Prostatic Hyperplasia (BPH) and Overactive Bladder (OAB) after 12 weeks of treatment. The primary outcome will be a change in the number of voidings and intensity of urgencies over 24 h using a micturition diary, and the secondary outcomes will be a change in lower urinary tract symptoms, a change in incontinence quality of life, a change in patients’ global impression of improvement, and a lower incidence of adverse events. A randomized intervention parallel multicenter study will be conducted in collaboration with 45 urological clinics at the national level. Patients will be assigned at a 1:1 ratio to the experimental and control groups using simple randomization according to odd and even patient sequence numbers in each ambulatory clinic. The experimental group will receive oral silodosin at a daily dose of 8 mg once daily and pelvic floor muscle training (PFMT) 5 times a week for 20–30 min a day, for 12 weeks. The control group will receive oral treatment with silodosin at a daily dose of 8 mg once daily for 12 weeks. The study protocol presents the starting points and design of a randomized, interventional, parallel, multicenter study looking at the effect of a combination of silodosin and PFMT versus silodosin treatment in men with BPH and OAB.

## 1. Introduction

The International Society for Continence (ICS) and the International Urogynecological Society (IUGA) define overactive bladder (OAB) as urgency with frequent urination and nocturia with or without urgent incontinence in the absence of a urinary tract infection or other disease [1]. All of these symptoms contribute significantly to the deterioration of quality of life for both sexes. An EPIC study estimated the prevalence of lower urinary tract symptoms (LUTS) in men and women using ICS definitions. The prevalence of male urinary storage symptoms (51%) was higher than the prevalence of urinary emptying symptoms (25%) and post micturition symptoms (16%). The overall prevalence of OAB was 11.8% in both sexes, and its frequency increased with age [2]. Lower urinary tract symptoms (LUTS) due to benign prostatic hyperplasia (BPH) are common in aging men and cause a deterioration in the quality of life [3].

The choice of LUTS treatment for BPH depends on clinical findings, treatment efficacy, treatment preferences, and patient expectations in terms of rate of onset, efficacy, side effects, quality of life, and disease progression. The first-choice therapy for male patients with LUTS and BPH is behavior modification, either with or without alpha-blockers. Conservative treatment (i.e., distraction techniques and bladder retraining) followed by anticholinergics is recommended when OAB symptoms persist after the administration of alpha-blockers [4]. Anticholinergics are the second-choice drug treatment for OAB symptoms.

Silodosin is highly selective for α1A-adrenoreceptors, which occur in the prostate, prostatic urethra, bladder base, and bladder neck. The inhibition of α1A-adrenoreceptors causes smooth muscle relaxation in these tissues and reduces bladder output obstruction. The effect is to alleviate lower urinary tract symptoms caused by BPH [5,6,7].

According to the Cochrane Urology Group, the method of the first treatment for overactive bladder in men with BPH and LUTS is pelvic floor muscle training (PFMT). PFMT is a method based on scientific evidence. It is defined as the repeated contraction and relaxation of the pelvic floor muscles. In symptoms of OAB in men, it is important to manage the suppression of urgency through the contraction of the rectal muscles [8]. Not enough studies on the combination of silodosin and PFMT in men with BPH and OAB have been published in the literature. To ensure the maximum effect of the intervention, it is necessary to constantly modify the exercise programs and update the knowledge in the relevant guidelines. It is important that the PFMT is interesting and that patients are motivated to complete the training program.

Anti-cholinergics are the basic drug treatment for OAB symptoms as a secondary choice. This is evidenced by several clinical trials that have confirmed the subsequent relief of OAB in patients with BPH after initial treatment with alpha-blockers [7,9,10]. Matsukawa et al. [11] compared the efficacy of combination therapy with silodosin and mirabegron 50 mg or fesoterodine 4 mg in patients with persistent OAB symptoms. At three months, there was a more significant reduction in OAB in the fesoterodine group than in the mirabegron group.

In the literature, there is a lack of published studies that examine a combination of silodosin and PFMT in men with OAB.

Silva [8] in a Cochrane system review of studies from various databases (CENTRAL, MEDLINE, Embase, Web of Science, LILACS, ClinicalTrials.gov, and WHO ICTRP), described information from studies on the effect of physical activity in men with BPH and LUTS. He included six randomized studies with 652 men over the age of 40 with mild to severe LUTS symptoms. The interventions were pelvic floor muscle training and Tai-chi. However, the quality of these studies was low, and the results were insufficient in terms of training the pelvic floor muscles for LUTS symptoms. The authors of the study point to the need for other high-quality randomized studies.

### 1.1. Primary Goal

The primary goal of this trial is to assess the efficacy of combination therapy with silodosin and pelvic floor muscle exercise (PFMT) versus silodosin treatment in men with BPH and OAB, according to the change in the number of voidings and intensity of urgencies over 24 h using a micturition diary, over 12 weeks of treatment.

### 1.2. Secondary Goals

The secondary goals are to assess changes in lower urinary tract symptoms (LUTS) using the International Prostate Symptom Score (IPSS), changes in incontinence quality of life using the Overactive Bladder Questionnaire (OAB-q), changes in the patient’s global impression of improvement, and the incidence of adverse events in the combined silodosin and pelvic floor muscle training compared to silodosin treatment alone over 12 weeks of treatment.

## 2. Materials and Methods

### 2.1. Study Design

The Silodosing study is designed as a randomized controlled intervention and parallel phase IV study. The Silodosing study will compare the effect of silodosin treatment and combination treatment with silodosin and PFMT in men with BPH and OAB treated with silodosin. The hypothesis is that after 12 weeks of combination therapy, the experimental group will have significantly fewer episodes in the number of voidings and intensity of urgencies over 24 h, a reduction in the prostate symptom score, and improvements in incontinence quality of life and patient global impression of improvement. The protocol was approved by the Ethics Committee of the University Hospital in Martin, Slovakia, Comenius University, number 09072020. All important protocol modifications will be approved by the same ethics committee. Informed consent will be obtained from trial participants by the local clinic of urology. Personal information about potential and enrolled participants will be collected, shared, and protected in concordance with Slovakian law.

### 2.2. Allocation

The Silodosing study will be performed with 45 urological outpatient clinics at the national level. It will be carried out in two parallel groups: the experimental group (E) and the control group (C). It will be a randomized controlled study with a 1:1 allocation ratio. Computer-generated sequences will be used for the allocation process by a researcher who will not participate in the study. The computer will generate an even and odd patient number. Odd-numbered patients will be given silodosin monotherapy at a dose of 8 mg once daily for 12 weeks, while even-numbered patients will receive combination treatment with silodosin at a dose of 8 mg once a day and pelvic floor muscle exercises at the same time. The generated numbers will be placed in sealed envelopes. Each envelope will contain the code of the experimental (E) group and control (C) group. The blinding will prevent deliberate selection (Table 1).

### 2.3. Sample Size Estimation

We used an estimate made by sampling the number of probands based on a power of test using 0.80 and alpha 0.05 (type I error). Using a statistical program, we determined the calculation of the number of probands; there will be 63 in the experimental group and 63 in the control group. We expect a 20% loss, so we will include at least 158 probands. According to the sample selection, we expect a 20% decrease in incidence after the intervention.

### 2.4. Inclusion Criteria

Willing to provide written informed consent. Men over 50 years with lower urinary tract symptoms, overactive bladder, and benign prostatic hyperplasia. Persistence of overactive bladder despite 4 weeks of silodosin treatment. Symptoms of overactive bladder (urinary frequency and urgency with or without urinary incontinence) for ≥3 months prior to Visit 1. Willing and able to complete the 3-day voiding diary and questionnaires. International Prostate Symptom Score (IPSS) score ≥8. Experience an average of 8 or more micturitions per day over the 3-day diary period. Experience an average of 2 episodes of urgency per day (grade 3 or 4) over the 3-day diary period.

### 2.5. Exclusion Criteria

Post-void residual volume (PVR) >200 mL. Evidence of urinary tract infection and hematuria. Use of anti-cholinergics or beta 3 mimetics within 4 weeks prior to Visit 1 and during the study. Oncological diseases of the lower urinary tract and prostate. Neurogenic bladder. Urethral strictures and bladder neck stenosis. Urolithiasis. Diabetes mellitus. Previous surgery of lower urinary tract. Stress urinary incontinence. Intermittent catheterization. Chronic urinary tract infection. Previous Botox treatment in the last 12 months. Chronic electrostimulation treatment of OAB in the last 12 months. Patient began or has changed a bladder training program or pelvic floor exercises less than 90 days before enrolment (T0). Cognitive deficits and dementia. Man has participated in an interventional trial within 30 days prior to enrolment (T0). Total daily urine production over 2500 mL according to voiding diary.

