### 2.6. Procedures

#### 2.6.1. Experimental and Control Groups

Continuation of silodosin treatment at a dose of 8 mg daily for 12 weeks.

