#### 2.6.2. Experimental Group

Peroral treatment with silodosin at a dose of 8 mg daily. 

Behavioral intervention: pelvic floor muscle training (PFMT) with urgency-suppression techniques.

The urologist will evaluate the strength of the rectal muscles before and after intervention by digital rectal examination (DRE). PFMT intervention will be performed by a trained physiotherapist, who will explain the correct exercise technique. Muscle strength and intra-anal endurance will be tested. PFMT will be conducted 5 days a week and supervised by a physiotherapist once a week. If the patient is able to perform PF muscle contractions correctly, they will be allowed to continue with the exercises at home (Table 2).

Education about proper urination training in the period without pathological urgency;Education in urgency-suppression techniques:Urgency-suppression techniques are methods/maneuvers that are used to decrease the feeling of urgency. They include (but are not limited to): distraction; PFM contraction; perineal pressure such as sitting on a hard chair; relaxation; breathing; toe-curling; and plantar flexion of the ankle [12];Education on the principle and effect of PFMT;Education about proper ergonomics during everyday activities;Education about the correct breathing stereotype;Exercise about pelvic floor muscle awareness;Exercises of varying intensity of the pelvic floor muscles in different positions;Pelvic floor muscle relaxation exercises.

Exercise 5 times a week for 30 min a day, for 12 weeks.

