The intervention in both groups will be oral treatment with silodosin at a daily dose of 8 mg; in the experimental group, pelvic floor muscle training (PFMT) with the suppressive urgency technique will be added. Interventions will last 12 weeks, with exercises five times a week for 30 min a day, under the supervision of a physiotherapist. Education will consist of education about proper urination training in the period without pathological urgency, education about conscious urgency suppression through the PFMT suppressive urgency technique, education on the principle and effect of PFMT, education about proper ergonomics during everyday activities, education about the correct breathing stereotype, and education regarding the correct understanding of exercises by physiotherapists in cooperation with a nurse.

The program includes exercises about pelvic floor muscle awareness, exercises of varying intensity of pelvic floor muscles in different positions, and pelvic floor muscle relaxation exercises. Subsequently, the exercise will be performed at home with a diary check.

Based on similar studies, we expect good cooperation, small losses of probands, and agreement with the study protocol. Patients who are assigned to silodosin only will be offered the opportunity to exercise after 12 weeks of treatment. We assume a 20% loss. We will consider the success of the treatment to be a decrease of more than 50% in remission.

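### The 90-day rule on prior pelvic floor exercise admits men already on a stable programme to both arms, which can dilute the PFMT contrast

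*Protocol article*

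**What the plan says.** Section 2.5 of the protocol article lists this exclusion: "Patient began or has changed a bladder training program or pelvic floor exercises less than 90 days before enrolment (T0"). Nothing else in sections 2.4 or 2.5 addresses current pelvic floor exercise or bladder training.

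Section 2.6.2 defines what the experimental arm adds: "Behavioral intervention: pelvic floor muscle training (PFMT) with urgency-suppression techniques". Section 2.6.1 gives the treatment common to both arms as "Continuation of silodosin treatment at a dose of 8 mg daily for 12 weeks" and does not mention exercises that a man may already be doing. Section 3 shows that controls are meant to go without the training during the trial: "Patients who are assigned to silodosin only will be offered the opportunity to exercise after 12 weeks of treatment".

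For the secondary point, section 2.5 also lists "Use of anti-cholinergics or beta 3 mimetics within 4 weeks prior to Visit 1 and during the study". Entrants must show "Persistence of overactive bladder despite 4 weeks of silodosin treatment", and the Introduction says that conservative treatment "followed by anticholinergics is recommended when OAB symptoms persist after the administration of alpha-blockers".

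**The concern.** A rule that accepts a therapy if it has been stable for 90 days suits background treatment that is not under test. Here it is applied to the therapy under test. A man who has trained unchanged for longer can be randomised. If allocated to control, he may go on training, so his arm is not silodosin alone. If allocated to the experimental arm, he has overactive bladder despite some form of the treatment and may have less to gain from being taught it.

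Such men are plausible on the article's own account. The Introduction places behaviour modification among first-choice options, recommends bladder retraining when symptoms persist on an alpha-blocker, and describes PFMT as a first treatment. The more of them enter, the closer the between-arm difference moves to zero and the lower the power.

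The drug criterion raises a separate issue. Use after entry is an event following randomisation, so it cannot decide who enrols. If it were applied by removing randomised men, the removals could be related to outcome and to arm.

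**Working it through.** **Inputs from section 2.3:** 63 men per arm, 20% loss, at least 158 enrolled, and a calculation "based on a power of test using 0.80 and alpha 0.05 (type I error"). Sidedness, SD and control rate are not given; the expected effect is described only as a 20% decrease in incidence.

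**The plan's own figures.** Enrolment is (63 + 63) / (1 − 0.20) = 126 / 0.8 = 157.5, rounded up to 158. This reproduces exactly.

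The 63 per arm cannot be derived from the stated inputs alone. With an assumed standardised difference d = 0.5 and a two-sided test, n = 2 × (1.960 + 0.842)² / d² = 15.70 / 0.25 = 62.8, so 63 (64 by the t distribution). Some pairs of proportions also come close: 0.30 v 0.10 or 0.90 v 0.70 gives 62. So d = 0.5 fits, but it is an assumption.

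**Dilution.** Let f be the share of entrants already on a stable programme, and suppose (worst case) that they show no difference between arms. Then:

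- d(f) = 0.5 × (1 − f)
- power = Φ(d(f) × √(63/2) − 1.960), with √31.5 = 5.612
- for f = 10%: d = 0.45, and Φ(2.526 − 1.960) = Φ(0.566) = 71.4%

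| f (assumed) | d | Power at 63 per arm | n per arm for 80% | Enrolment after 20% loss |
|---|---|---|---|---|
| 0% | 0.500 | 80.1% | 63 | 158 |
| 2% | 0.490 | 78.5% | 66 | 165 |
| 5% | 0.475 | 76.0% | 70 | 175 |
| 10% | 0.450 | 71.4% | 78 | 195 |
| 20% | 0.400 | 61.2% | 99 | 248 |

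The t distribution gives 79.5%, 70.7% and 60.6% at f = 0%, 10% and 20%, less than one point lower in each case.

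**If these men still gain.** If they obtain a fraction g of the full benefit, d = 0.5 × (1 − f(1 − g)). With f = 10% and g = 0.5, d = 0.475 and power is 76.0%, the same as f = 5% with no gain.

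**Drug use after entry.** No calculation is possible. The documents give neither a rate by arm nor the handling of men who start such a drug, and section 2.9 names no analysis set.

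**The case against.** **On the 90-day rule.** A reader might infer that the criterion biases the comparison. It does not: allocation is random, so stable trainers are expected equally in both arms. The trial would still estimate without bias the effect of adding the taught programme in the men enrolled; that effect would simply be smaller than in men not already training.

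The outcome is change from T0, so a control who keeps an unchanged programme already has its effect in his baseline and need not change further. That is fair. It places the dilution mainly in the experimental arm, where such a man may improve less, and it does not remove it.

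The randomised package is also fuller than many existing programmes are likely to be: taught and supervised weekly by a physiotherapist, five days a week, in phases, with urgency suppression. Every entrant must still average at least 8 micturitions and 2 high-grade urgency episodes a day, so there is room to improve. The assumption of no added benefit is therefore an upper limit on the loss. The share is unknown, and at 2% the loss is under two points.

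**On the drug criterion.** A stronger reading is that the rule removes randomised men who start an anticholinergic or beta-3 drug, mostly controls, and so biases the result. The documents do not support this. Nowhere do they say that such a man is withdrawn or left out of the analysis. The phrase may be a prohibited-medication rule condensed into the list, with its handling in the full protocol or analysis plan, which are not shown. The Introduction puts anticholinergics after conservative treatment, a step the article does not say controls have had, so it does not show that controls would start them more often. What stands is that the phrase sits in an eligibility list, where it cannot operate as written.

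**Conclusion.** The main point holds as one of dilution. The criterion, as worded, lets men already receiving a form of the randomised component into a comparison meant to be against silodosin alone, and no other stated criterion keeps them out.

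If such men are 2% to 20% of entrants, power at 63 per arm falls from about 80% to between 78.5% and 61%. This rests on three assumptions that the documents do not settle: a 0.5 SD effect, the share itself, and no added benefit in these men. The loss is negligible if few enrol, and material from about 5% to 10% upwards.

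The drug criterion is a secondary point of drafting. Bias would follow only if the phrase were used to remove randomised men, which is not stated.

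**What to change.** Reword the exclusion as: *Any pelvic floor muscle training or bladder training programme in the 90 days before enrolment (T0).* This still covers the men whom the present wording keeps out and closes the gap. It costs one edit and the loss of a few men on long-standing programmes. With f = 0, the planned 63 per arm and 158 in total need no change on this account.

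For the drug criterion, leave any clinical restriction on these drugs as the investigators intend it, but move the part that concerns the period after entry out of the eligibility list. State that randomised men who use such a drug are followed to the T12 diary and analysed in their allocated arm, and report their number by arm. This costs a sentence or two and no extra visits, since T12 assessments are already scheduled in Table 1.

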### 2.6. Procedures

#### 2.6.1. Experimental and Control Groups

Continuation of silodosin treatment at a dose of 8 mg daily for 12 weeks.

#### 2.6.2. Experimental Group

Peroral treatment with silodosin at a dose of 8 mg daily. 

Behavioral intervention: pelvic floor muscle training (PFMT) with urgency-suppression techniques.

The urologist will evaluate the strength of the rectal muscles before and after intervention by digital rectal examination (DRE). PFMT intervention will be performed by a trained physiotherapist, who will explain the correct exercise technique. Muscle strength and intra-anal endurance will be tested. PFMT will be conducted 5 days a week and supervised by a physiotherapist once a week. If the patient is able to perform PF muscle contractions correctly, they will be allowed to continue with the exercises at home (Table 2).

Education about proper urination training in the period without pathological urgency;Education in urgency-suppression techniques:Urgency-suppression techniques are methods/maneuvers that are used to decrease the feeling of urgency. They include (but are not limited to): distraction; PFM contraction; perineal pressure such as sitting on a hard chair; relaxation; breathing; toe-curling; and plantar flexion of the ankle [12];Education on the principle and effect of PFMT;Education about proper ergonomics during everyday activities;Education about the correct breathing stereotype;Exercise about pelvic floor muscle awareness;Exercises of varying intensity of the pelvic floor muscles in different positions;Pelvic floor muscle relaxation exercises.

Exercise 5 times a week for 30 min a day, for 12 weeks.

### 2.7. Outcome Measures

#### 2.7.1. Primary Outcomes

Change in the number of voidings and intensity of urgencies over 24 h using a voiding diary. Voiding diary includes voided volume over 24 h (mL), the number of voidings per 24 h, voided volume during the day (mL), the number of voidings per day, voided volume during the night (mL), night-time frequency (nocturia), and mean voided volume per 24 h, during the day and during the night (mL) for 3 days, and the mean values were used.

The Patient Perception of Intensity of Urgency Scale (PPIUS) evaluates the severity of symptoms of an overactive bladder: 0 = no urgency, retaining urination for a very long time without fear of voiding; 1 = moderate urgency, able to hold urine as long as necessary without fear of voiding; 2 = moderate urgency, able to hold urination for a short while without fear of voiding; 3 = serious urgency, unable to hold urine; 4 = urgency urinary incontinence, urine leakage occurs before reaching the toilet. Reliability and validity are 0.95, and Spearman’s correlation is 0.89 [13].

The definition of an overactive bladder (OAB) is when patients have an urgency 1 or more times a day, voiding 8 or more times a day, and nocturia 2 or more times at night, with or without urgency urinary incontinence [1].

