## 3. Conclusions

The study protocol presents the starting points and design of a randomized, interventional, multicenter study monitoring the effect of combination therapy with silodosin and pelvic floor muscle training (PFMT) in comparison with silodosin treatment alone in men with BPH and OAB. The study may provide evidence of the efficacy of combined treatment for OAB and indicate an active approach for the treatment of OAB through exercise. The strength of the study is that it promotes a non-invasive and conservative treatment of strengthening pelvic floor muscles with the suppressive-urgency technique in addition to silodosin treatment. We will use standardized measuring tools: the voiding diary for the assessment of changes in the number and intensity of urgencies over 24 h [1], the Patient Perception of Intensity of Urgency Scale (PPIUS) [13,19,21], the International Prostate Symptom Score (IPSS) for the assessment of prostate symptoms [13,14], the Overactive Bladder Questionnaire (OAB-q) for assessing changes in incontinence quality of life [16,17], the Overactive Bladder Symptom Score (OABSS) to examine the symptoms of an overactive bladder [18], and the Patient Global Impression of Improvement score (PGI-I) to assess the condition of urinary problems compared to pre-treatment [22].

The strength of the study is its support of the innovative non-invasive conservative treatments of pelvic floor muscle training and medication with silodosin in patients with BPH and OAB.

The Methodology section describes the ranking criteria, method of inclusion in the study, and randomization procedure. The patients will be men aged over 50 with BPH and OAB. Within that demographic, the following parameters will be monitored: age of probands, education, height, weight, employment, smoking, alcohol, hypertension, lung diseases, nervous diseases, cardiovascular diseases, and other diseases.

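### Two primary outcomes share one alpha and one power figure with no rule for a positive trial, so the 5% and the 80% cannot both be relied on

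*Protocol article*

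**What the plan says.** The same pair of measures appears in four places in the protocol article.

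- Abstract: "The primary outcome will be a change in the number of voidings and intensity of urgencies over 24 h using a micturition diary".
- Primary Goal (1.1): efficacy is judged "according to the change in the number of voidings and intensity of urgencies over 24 h using a micturition diary".
- Study Design (2.1): the experimental group is expected to have "significantly fewer episodes in the number of voidings and intensity of urgencies over 24 h".
- Primary Outcomes (2.7.1), under a plural heading: "Change in the number of voidings and intensity of urgencies over 24 h using a voiding diary".

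The sample size (2.3) is "based on a power of test using 0.80 and alpha 0.05 (type I error". It comes to 63 per group, raised to 158 in total for a 20% loss. The expected effect is a 20% fall in an unnamed incidence. Statistical Analysis (2.9) sets the threshold at p < 0.05 as a general level, with no division of alpha and no testing order. The only statement of what counts as success is in the Conclusions: a fall of over 50%, worded as a fall in remission and linked to neither primary measure.

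The urgency measure is described in more than one way. Section 2.7.1 says "The Patient Perception of Intensity of Urgency Scale (PPIUS) evaluates the severity of symptoms of an overactive bladder" and lists its grades 0 to 4, but does not say how grades from many voids become one value per patient. The Conclusions refer to "the voiding diary for the assessment of changes in the number and intensity of urgencies over 24 h", which adds a count of urgencies and leaves out voidings. Eligibility (2.4) uses a count: "Experience an average of 2 episodes of urgency per day (grade 3 or 4) over the 3-day diary period".

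**The concern.** With two primary outcomes, the meaning of a 5% error rate and of 80% power depends on what counts as a positive trial. If success on either outcome is enough and each is tested at 5%, the trial has two chances of a false claim. If both must succeed, it has to clear two hurdles, and a size set for one is too small for the pair. The article fixes alpha, power, sample size and threshold but not this rule, so the choice could be made after the results are known. The sponsor could then claim success on whichever outcome reached significance, or miss a real effect because both were required.

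The loose description of urgency adds a separate problem. Without one stated summary of the scale, the second primary outcome is not a single defined quantity.

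**Working it through.** **Inputs from the protocol article.** Two primary measures (2.7.1); alpha 0.05, power 0.80, 63 per group, 20% loss, 158 in total (2.3); p < 0.05 (2.9).

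**Inputs assumed.** Two-sided testing; each outcome has 80% power on its own; the two test statistics are bivariate normal with correlation r. The documents give no r, so 0, 0.5 and 0.8 are shown.

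**Step 1: the plan's own figures.** The total reproduces: 2 × 63 = 126, and 126 / (1 − 0.20) = 157.5, rounded up to 158. The 63 per group cannot be derived from the stated inputs, because the 20% fall has no baseline, standard deviation or named outcome. It does match a comparison of two means on one outcome at an assumed standardised difference of 0.5:

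n = 2 × (1.960 + 0.842)² / 0.5² = 62.8, so 63 per group (64 with the t distribution).

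Some comparisons of two proportions also come close, for example 62 per group for 0.30 against 0.10. Every route found is a calculation for one outcome.

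**Step 2: either outcome suffices, each at 5%.**

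- Familywise error = 1 − P(both |Z| < 1.960). At r = 0 this is 1 − 0.95² = 0.0975.
- Power for at least one = 1 − P(both miss). At r = 0 this is 1 − 0.20² = 0.96.

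**Step 3: both outcomes must succeed, each at 5%.**

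- Error is at most 5%, because a false claim requires the outcome with no effect to be significant at 5%.
- Power = P(both significant). At r = 0 this is 0.80² = 0.64.

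For r > 0 the same probabilities come from the bivariate normal distribution.

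| r | Either: familywise error | Either: power | Both: error | Both: power |
|---|---|---|---|---|
| 0 | 9.75% | 96% | at most 5% | 64% |
| 0.5 | 9.1% | 91% | at most 5% | 69% |
| 0.8 | 7.8% | 87% | at most 5% | 73% |

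**Step 4: size needed if both must succeed.** With a standardised difference of 0.5 on each outcome, 80% joint power needs 83, 79 or 74 per group at r = 0, 0.5 or 0.8. After 20% loss the totals are 166 / 0.8 = 207.5, so 208; 158 / 0.8 = 197.5, so 198; and 148 / 0.8 = 185. The plan has 158. The success rule therefore determines the sample size.

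**The case against.** The analysis plan is not shown and this is a condensed article. Handling of multiple outcomes is often left to the analysis plan, so the absence of an adjustment method is not in itself a finding. That stands. But section 2.3 itself states a power and a size, and which outcome they refer to is a protocol decision. A later multiplicity rule could protect the 5%; it would not show that 63 per group gives 80% power for both outcomes.

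The Abstract's singular *outcome* could mean one combined endpoint, but no combination is defined. The *and* in the hypothesis gives little support to a both-must-succeed rule, because the same sentence goes on to list the symptom score, quality of life and global impression. The figures do rest on an assumed correlation and on 80% power per outcome, and the error inflation shrinks as the correlation rises.

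A reader might infer three stronger points, none of which the documents support.

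- *Neither stated rate holds.* Under each rule exactly one fails. Either-suffices inflates error but leaves power at 87% to 96%; both-must-succeed lowers power but keeps error at or below 5%.
- *The Conclusions wording alters the error rate.* It does not. It sits in a list of instruments and leaves the urgency measure unclear.
- *The urgency score can worsen in a patient who improves.* Averaging grades over voids could do this. A man going from 12 voids (two grade 3, ten grade 1) to 8 (two grade 3, six grade 1) moves from 16/12 = 1.33 to 12/8 = 1.50. But the averaging statement in 2.7.1 closes a list of diary items that does not include urgency, and no summary of the scale is stated. A daily sum for the same man falls from 16 to 12. The example shows only that the summary matters.

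**Conclusion.** The point holds in this form: two primary outcomes, one alpha and one power tied to neither, and no rule for a positive trial. Until a rule is fixed, the 5% and the 80% cannot both be relied on. Over correlations from 0 to 0.8, with 80% power assumed for each outcome, the cost is either a familywise error of 9.75% down to 7.8% or a joint power of 64% up to 73%. Since section 2.3 gives no inputs for either outcome, the actual power for each is unknown, and these figures show the size of the problem rather than the trial's exact operating characteristics. The undefined urgency summary and the different description in the Conclusions are a matter of definition, to be settled in the same edit.

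**What to change.** In sections 2.3, 2.7.1 and 2.9, state a fixed sequence at two-sided 5%. Number of voidings per 24 h is tested first, which follows the order the protocol already uses. The urgency outcome is tested only if the first result is significant. State that the 80% power refers to the number of voidings.

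If the intention is that both outcomes must succeed, say so and restate the power as about 64% to 73% under the assumptions above, or enlarge the trial as in Step 4.

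Under either rule, state one summary of the urgency scale per patient and use it throughout. Reconcile the Conclusions with the Abstract and sections 1.1, 2.1 and 2.7.1.

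**Cost.** The diary and scale data are unchanged, and the fixed sequence itself requires no more patients. Urgency can be claimed only after a significant result on voidings, so the chance of claiming it is the joint power in the table. The change alters the primary analysis and needs a protocol amendment; section 2.1 sends important modifications to the ethics committee. Choosing which outcome goes first is partly a judgement for the sponsor, but it must be made before the results are seen.
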